### Precautions for plasma separation

The plasma separation process shall be performed on ice to maintain the integrity of the blood cellsThe entire separation process will be completed within 4 hThe blood collection and plasma separation process will be handled carefully to avoid the risk of hemolysis

After the study, all samples will be safely destroyed.

### Statistical analyses

The dataset will include a safety set, a full analysis set (FAS), and a per-protocol set. The safety set is designed for participants who will be randomly assigned to receive at least one session of treatment. The FAS will include all medical data related to the trial and will indicate the intervention conducted; however, participants who miss the primary outcome evaluation will be excluded. In the per-protocol set, participants will be included if they receive at least three constant sessions of treatment.

In this trial, the FAS will be used for the basic analysis. For missing data, we will employ the imputation adjustment approach, and the last observation analysis will be selectively used to handle the missing data.

A sensitivity analysis will then be used to compare the results of the per-protocol analysis and the different intervention analyses to evaluate the impact of the missing data on the trial results.

Descriptive statistics about quantitative indicators, such as means, standard deviations, medians, minimums, and maximums, will be presented. Variance analysis will be used to compare the quantitative indices among the different groups (healthy control group and experimental groups 1 and 2), and the Student-Newman-Keuls test will be used to analyze the two subgroups.

Classification indicators will be described by the number and percentage of each category. The chi-squared test or exact probability method will be used to compare the qualitative indices among the three groups, and the chi-squared segmentation method will be used to compare the two pairwise subgroups.

SPSS version 21.0 will be used to analyze all trial data. All statistical tests will be double-sided, and statistical significance will be considered when the *p* value is ≤ 0.05.

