## Methods

### Study design

This is a prospective, multicenter, analyst-blinded, randomized controlled trial. Subjects will be grouped into one healthy control group and two parallel experiment arms, as follows: (1) people without PCOS (healthy control group), (2) patients diagnosed with PCOS based on clinical indices (experimental group 1), and (3) patients diagnosed with PCOS based on metabolomic indices (experimental group 2). A total of 276 participants, including 60 people without PCOS and 216 patients with PCOS, will be recruited. The 216 patients with PCOS will be randomly assigned to the two experimental (diagnosis) groups in a 1:1 ratio. After group assignment, medical detection results, relative information, and biological samples will be collected from all three groups. Additionally, the blood samples from all participants will be tested using metabolomic methods for further study, while the analysis results will be totally blinded to all participants and their research physicians. Based on our previous study [3], we will categorize patients with PCOS into two subgroups: patients with hormone metabolism disorders (subgroup 1) and patients with lipid metabolism disorders (subgroup 2).

The two diagnosis groups will be automatically divided into the two different subgroups according to patient characteristics. The main difference is that in group 1, diagnosis will be based on clinical indices [1], such as clinical signs and symptoms and ultrasonography findings, while in group 2, diagnosis will be based on metabolomic indicators. All patients will receive treatment according to their subtype group, and the treatment will consist of Diane-35 or metformin. The intervention period for all experimental groups will be 6 months, and the results will be evaluated after the completion of three constant treatment sessions (3 months).

Outcomes will be assessed, and the data will be analyzed by someone blinded to the assignment of participants. The study design is shown in Fig. 1, and the timeline is presented in Figs. 2 and 3.

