### Outcome measurements

The healthy control group will remain enrolled in the trial until all their samples are collected. For the experimental groups, the primary outcome will be the changes in their relative PCOS condition evaluated using clinical indices. The main clinical index that will be evaluated is the LH/FSH ratio.

Secondary outcomes will be assessed using other indices, signs, and symptoms, as described in the 2018 Chinese Endocrine Society clinical practice consensus on PCOS [1] such as sex hormone-related indices (FSH, LH, prolactin, estradiol, progesterone, testosterone, anti-Müllerian hormone (AMH), and vitamin D), blood lipid-related indicators (total cholesterol, triglycerides, HDL, LDL, Apo A1, Apo B, lipoprotein(a), free fatty acids, and high-sensitivity C-reactive protein), and endocrine-related indicators (glucose and insulin (at 0, 30, and 120 min) and blood uric acid). To help evaluate the outcomes, three metabolic markers will also be used, namely, palmitoyl sphingomyelin, cyclic guanosine monophosphate, and DHEAS. Ultrasound results will also be evaluated, and the number and diameter of follicles in both ovaries will be measured.

Safety outcomes will include any severe impairment in liver function or inability of the patient to tolerate symptoms (e.g., nausea and vomiting caused by metformin) related to the therapeutic drugs. Such outcomes will be monitored after each treatment session (1 month) using the hepatic function test. An exploratory outcome will be complete recovery from PCOS after treatment within 26 weeks.

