### Safety evaluation

AEs will be evaluated at every visit and will include any unexpected or unfavorable response that occurs during or after treatment. Although these events may not have a causal relationship with the variables in this study, the investigators will need to ensure that all AEs are reported and recorded in the subject’s medical records. In this trial, AEs are defined as disorders that (1) hinder one’s ability to work or are life-threatening (especially liver dysfunction) or (2) lead to hospitalization or prolong department or hospital stay. Remedial treatment should be given immediately to resolve any observed AE, and all AEs will be reported to the responsible units, ethical committees, and trial administrator to decide whether the participant ought to remain in or drop out of the trial. Regardless of the decision, all participants with an AE will be followed up until the event has been resolved or the condition has become chronic or stable.

The study should not cause any additional harm to the participants. In case of serious unexpected harm to a participant related to the study, we will shoulder the relevant expenses (including the diagnosis and treatment) and follow up the condition of the participant until recovery.

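### The safety set is tied to a one-month treatment session without saying whether it must be completed, and the protocol gives two incompatible definitions of an adverse event

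*Protocol article*

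**What the plan says.** **Safety population.** Statistical analyses, in the protocol article: "The safety set is designed for participants who will be randomly assigned to receive at least one session of treatment". The same section admits participants to the per-protocol set once they have received three or more uninterrupted sessions.

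**Length of a session.** Outcome measurements: "Such outcomes will be monitored after each treatment session (1 month) using the hepatic function test". Study design agrees: "the results will be evaluated after the completion of three constant treatment sessions (3 months").

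**Safety outcomes.** Outcome measurements lists severe liver impairment and "inability of the patient to tolerate symptoms (e.g., nausea and vomiting caused by metformin").

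**Adverse events.** Safety evaluation opens broadly: "AEs will be evaluated at every visit and will include any unexpected or unfavorable response that occurs during or after treatment". It obliges investigators to see that all AEs are reported and recorded. It then continues: "In this trial, AEs are defined as disorders that (1) hinder one’s ability to work or are life-threatening (especially liver dysfunction"). Its item (2) adds events that put the patient in hospital or lengthen a stay. Every AE is to receive immediate remedial treatment and to be reported to the responsible units, the ethics committees and the trial administrator, who decide whether the participant continues.

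**Early exit.** Subject dropout lets a participant leave because of an AE, with no minimum time on treatment. It also names serious AEs as a separate ground for removal.

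**The concern.** A safety population is normally entered at first exposure, so that anyone harmed early is in both numerator and denominator. Here entry is expressed in units of a month. A participant who takes metformin, cannot tolerate it and stops in week 2 has had one of the protocol's own safety outcomes, yet may not belong to the population in which that outcome is analysed. The wording also mixes assignment with exposure, since being assigned to receive a session is not the same as having received one.

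The two AE statements raise a separate problem. The second is introduced as the definition for this trial, so staff at the three centres could reasonably take it as the operative one. Nausea that is unpleasant but tolerated, and that neither impedes work nor leads to hospital, is an AE under one sentence and not under the other. Counts would then depend on which sentence a centre follows.

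At stake are the safety denominator, the intolerance rate and the AE tables. Both arms use Diane-35 and metformin but sort patients to them differently. A loss specific to one drug could therefore differ between arms if the drug mix differs.

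**Working it through.** The document gives no safety-set size, early-stopping rate or AE rate, so there is no stated figure to reproduce. The check sets the passages side by side and then shows arithmetic on labelled assumptions.

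**1. Length of a session.** Study design: 3 months / 3 sessions = 1 month. Outcome measurements gives 1 month directly. The two agree.

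**2. What the entry rule can mean.** Three readings are open:
- everyone assigned to treatment;
- everyone who started a session;
- everyone who received a whole session.

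The per-protocol set uses the same verb for three sessions, and Study design describes that three-session point as completion. By parallel, receiving one session most naturally means completing one month. Completion is nevertheless not written in the safety-set sentence, and no reading states the rule by first dose.

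**3. Whether first-month exits are foreseen.** They are. Subject dropout sets no minimum exposure. Study limitations excludes participants who miss seven consecutive days of treatment, which can happen in month 1.

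**4. Size on the completed-session reading.** Input from the document: 2 x 108 = 216 randomised. Assumption: a share e stops in month 1. Number left out = 216 x e.

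| Assumed e | Left out of 216 |
|---|---|
| 2% | 4.3, about 4 |
| 5% | 10.8, about 11 |
| 10% | 21.6, about 22 |

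**5. Effect on an intolerance rate.** Assumptions: true intolerance is 10%, so k = 0.10 x 216 = 21.6; a share s of it leads to stopping in month 1; nobody else stops in month 1. Observed rate = (k - s k) / (216 - s k).

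| Assumed s | Calculation | Observed rate |
|---|---|---|
| 25% | 16.2 / 210.6 | 7.7% |
| 50% | 10.8 / 205.2 | 5.3% |
| 75% | 5.4 / 199.8 | 2.7% |

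With entry at first dose, the rate stays at 10% in every row. On the readings that admit everyone assigned or everyone who started, nobody is lost for stopping early.

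**6. The two AE statements.** An event that is unfavourable but does not impede work, threaten life, or cause or prolong a hospital stay meets the opening sentence and fails the later one. Both cannot be the definition. Because Subject dropout speaks of serious AEs as something distinct from AEs, a further, undefined category sits above a definition that is already narrow.

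**The case against.** The strongest reply is that the safety-set sentence does not require completion, whereas Study design says completion when it means it. That stands: the defect is an ambiguity with one damaging reading, and an explicit exclusion of first-month stoppers is not stated.

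A reader might also infer that AEs are limited to serious events and that all non-serious harms vanish from the results. The document does not support this. The broad sentence and the duty to record all AEs remain in the text. Impeding work is a wider criterion than life-threatening or hospitalising events. Inability to tolerate symptoms is a safety outcome in its own right, whatever the AE definition. AE details go into case report forms, participants with an AE are followed to resolution or stability whether or not they stay in the trial, and symptoms can be reported during follow-up. None of that recording depends on the safety set. What remains at risk is narrower: milder, tolerated harms in the AE tables, and early stoppers in the analysed population.

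A difference in bias between arms is possible but not shown, since no drug split per arm and no stopping rate per drug is given.

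It can also be said that exact population rules are often left to an analysis plan. That would answer an omission. Here the protocol states a rule, and states it in a form that can be read in more than one way.

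**Conclusion.** The point holds as two defects of wording. First, the safety set is tied to a one-month session without saying whether it must be completed, and the reading most consistent with the per-protocol wording omits participants who stop in month 1. Second, Safety evaluation gives two incompatible AE definitions, so tolerated, milder harms may not be counted as AEs.

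The size cannot be derived from the document. The figure of about 4 to 22 of 216 needs both an assumed 2-10% first-month stopping rate and the completed-session reading. The intolerance rates of 7.7%, 5.3% and 2.7% need an assumed true rate of 10% and the assumed timing as well.

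Severity is moderate. The primary LH/FSH analysis uses the full analysis set and is not touched.

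**What to change.** 1. In Statistical analyses, define the safety set as all randomised participants who take at least one dose of study drug, summarised by arm and by drug received.
2. In Safety evaluation, use the broad definition for recording and tabulating AEs. Give items (1) and (2) their own label as a more severe category.
3. Reconcile Subject dropout, Outcome measurements and Safety evaluation, so that it is clear which category triggers reporting, remedial treatment and the decision on continuation. Relabelling alone would send every minor event through those steps. Which category should trigger them is a clinical decision for the sponsor, and this review does not make it.

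The cost is a few sentences, slightly more AE recording and higher reported AE rates. Trial status gives recruitment as complete in August 2019. The set definition can still be settled before data lock, but mild events not captured so far would have to be sought in the medical records.

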### Subject dropout

Subject dropout occurs when:
The subject quits the studySafety issues arise (e.g., adverse events (AEs), failure of contraceptive measures, accidents)The subject is lost to follow-upResearchers remove the subject from the trial due to poor compliance, severe liver dysfunction, complications, or serious AEs

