#### Clinical index group

For the clinical index group, blood samples and medical information of all eligible participants will be collected. Based on several guidelines and clinical experience, subgroup 1 (participants with hormone metabolism disorders) will receive orally administered Diane-35 once a day for 21 days, after which the treatment will be paused for 7 days. Subgroup 2 (participants with lipid metabolism disorders) will receive orally administered metformin (2000–2500 mg) once a day based on their clinical condition. The entire treatment period will be at least 6 months. During the trial, blood samples will be collected three times (week 0, week 15 ± 1, and week 26 ± 1) for metabolomic evaluation to assess changes. However, the detection information will be blinded to all participants and clinical research physicians to avoid influencing the results. All clinical research physicians will be required to have majored in endocrinology and metabolism or gynecological endocrinology for at least 10 years. They must also be employed as an attending physician for > 5 years. Finally, they must receive professional training on clinical trials and pass a test to ensure consistent performance in the study methods.

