### Study limitations

The main difficulty inherent to this trial is making a consistent diagnosis in experimental group 1 because the diagnosis will be made by several different physicians. To address this problem as much as possible, our group will organize a diagnosis team consisting of three professional physicians who have majored in endocrinology and metabolism or gynecological endocrinology for at least 10 years and achieved the position of assistant director . If the clinical research physicians cannot diagnose the participant’s subtype, the case will be submitted to the team for a final diagnosis. Another methodological difficulty is ensuring that the treatment complies with the scheme. In this trial, we will ensure that medication reminders are sent and participants who miss treatment for seven consecutive days will be excluded from the trial.

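### The full analysis set leaves out randomised patients who lack the primary outcome, so the main comparison rests on observed outcomes and the stated imputation does not bring those patients back

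*Protocol article*

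**What the plan says.** The protocol article, Statistical analyses, names the analysis set for the main result: "In this trial, the FAS will be used for the basic analysis". The paragraph before it limits that set: "participants who miss the primary outcome evaluation will be excluded". For missing data, the same section says that "we will employ the imputation adjustment approach, and the last observation analysis will be selectively used to handle the missing data". The check on missing data reads: "A sensitivity analysis will then be used to compare the results of the per-protocol analysis and the different intervention analyses". The per-protocol set in that section is defined only by having received three uninterrupted treatment sessions.

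Two other sections create missing outcomes. Subject dropout counts it as dropout when researchers "remove the subject from the trial due to poor compliance". Study limitations adds that "participants who miss treatment for seven consecutive days will be excluded from the trial". No section says that patients removed in this way are still measured or stay in the FAS.

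Outcome measurements names the LH/FSH ratio as the main index but gives no time point. Study design describes a 6-month intervention and an evaluation after three sessions (3 months). Sample size calculation allows for dropout of up to 20%.

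**The concern.** Randomisation protects the comparison only while patients are analysed as allocated. Here a patient can leave the main analysis because of something that happens after allocation: not tolerating the drug, not taking it, or not returning. The name FAS suggests an as-randomised analysis, but the definition gives an observed-outcome one.

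The exclusions need not be neutral between arms. Treatment follows subtype, and subtype is assigned by a different method in each arm, so the mix of Diane-35 and metformin can differ between them. Outcome measurements itself names metformin nausea and vomiting as a tolerance problem. Removal for poor compliance is a researcher's decision, and under Blinding the physicians are blinded to the group 1 assignment but can see diagnostic and treatment allocation data for group 2.

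The stated safeguards do not meet this. Imputation cannot act on the primary outcome of patients who are already outside the set. Selective use of the last observation, with no criterion given, leaves room to choose the method after the data are seen.

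**Working it through.** **Step 1. What can be imputed for the primary outcome?** The article fixes no time point for LH/FSH, so each reading is tried.

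- *Evaluation at month 3* (Study design). Every FAS member has the month-3 value by definition. Later values may be missing, but they are not the primary outcome.
- *Evaluation at month 6* (end of the intervention). A patient measured at week 15 but not at week 26 has missed the evaluation and is excluded, so nothing is carried forward.
- *Exclusion only if there is no post-baseline value.* Week 15 could then be carried to week 26, and imputation does some work. Patients with no post-baseline value are still excluded. This reading assumes that LH/FSH is measured at both weeks. The text describes those blood samples as metabolomic, and the full schedule is in Fig. 3, which is not shown.

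The text speaks of one primary outcome evaluation, which fits the first two readings better. Under all three, some randomised patients are left out of the main analysis.

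**Step 2. Does the stated check test the missing-data assumption?** It compares results from the per-protocol analysis and from other intervention analyses that are not defined. The per-protocol set selects on treatment received. Moving between sets changes who is analysed. It does not change what is assumed about the outcomes that were not observed.

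**Step 3. How many patients?** Inputs from Study design and Sample size calculation: 216 randomised, 108 per arm, dropout up to 20%, significance level 0.05, power 0.80. Tests are two-sided (Statistical analyses).

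- The plan's 216 cannot be reproduced, because no LH/FSH effect size or SD is given. That is a separate matter, and only the dropout arithmetic is needed here.
- Left out at the maximum: 216 × 0.20 = 43.2, so up to 43.
- Remaining: 216 × 0.80 = 172.8, or 108 × 0.80 = 86.4 per arm, about 86.
- Detectable standardised difference: d = (1.960 + 0.842) × √(2/n).
  - n = 86: 2.802 × √(2/86) = 0.43 SD.
  - n = 108: 2.802 × √(2/108) = 0.38 SD.

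The 0.38 SD applies if the outcome is actually measured in all 108 per arm. Imputation alone would not fully recover it.

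**Step 4. How large could the bias be?** Let p be the share left out of each arm, and g the mean outcome of those left out minus that of those measured, in SD and equal in both arms. The measured mean differs from the full-arm mean by −p × g. The arm difference is therefore biased in absolute size by |p_A − p_B| × |g|. Neither p by arm nor g is in the article, so these values are assumptions:

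| Dropout by arm | g (SD) | Bias (SD) |
|---|---|---|
| 20% vs 20% | any | 0 |
| 15% vs 25% | 0.25 | 0.10 × 0.25 = 0.025 |
| 15% vs 25% | 0.5 | 0.10 × 0.5 = 0.05 |
| 15% vs 25% | 1.0 | 0.10 × 1.0 = 0.10 |

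If g differs between arms, the bias is |p_A × g_A − p_B × g_B|, and equal dropout rates alone do not make it zero.

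**The case against.** **Imputation still has a role.** The sentence on missing data is general. It can apply to the many secondary indices, and to week 26 on the third reading above. This stands. A reader might infer that imputation has nothing at all to do, or that the two rules flatly contradict each other. The text supports only the narrower statement, that on the plain reading imputation cannot restore excluded patients for the primary outcome.

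**The FAS is not a set of treatment completers.** A patient with fewer than three sessions who was measured belongs to it. This also stands: membership depends on having the outcome, not on finishing treatment.

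**The per-protocol set is not simply a smaller FAS.** A reader might take it as a further selection from the FAS. If the evaluation is at month 6, a patient who leaves between months 3 and 6 could be per-protocol and yet outside the FAS. The weakness of the check is that it varies no missing-data assumption, and this does not depend on nesting.

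**The seven-day rule and the Diane-35 schedule.** Both involve seven days, and a reader might see a conflict with the text "after which the treatment will be paused for 7 days" in Clinical index group. That pause is scheduled, so observing it is not missed treatment. The equal number is no contradiction.

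**Differential dropout may be small.** Both arms use the same two drugs, and participants are blinded to their group. Drug mix can separate the arms only through patients whom the two methods would classify differently. This is a fair limit on the likely bias, and large figures should not be read into the plan. It does not remove the route through researcher-decided removal.

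**An unseen SAP or full protocol may say more.** It may specify the model or continued follow-up. The point does not rest on such omissions. It rests on a stated exclusion, which a fuller document would have to override.

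**Conclusion.** The point holds in this form. As written, the main analysis excludes randomised patients according to whether the primary outcome was obtained. The trial's removal rules can produce such absences, and neither the imputation sentence nor the stated sensitivity analysis addresses the resulting selection for the primary outcome.

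The firm figures are an upper limit of 43 of 216 left out at the plan's own 20% maximum, and a detectable difference of about 0.43 SD with 86 per arm against 0.38 SD with 108. The 20% is a tolerance, not a forecast. The 0.025 to 0.10 SD bias is an illustration that rests on an assumed 10-point dropout gap and an assumed difference between dropouts and measured patients. It is zero if both the rate of dropout and the kind of patient who drops out are the same in each arm. A reader might infer that the result is known to be biased by a material amount. The document gives no data on dropout by arm and does not support that. What it shows is a rule that permits bias, with no adequate check for it.

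**What to change.** Before database lock, amend the Statistical analyses section and the matching dropout text:

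1. Define the FAS as all randomised patients, analysed in their assigned arm.
2. State the time point of the primary LH/FSH evaluation.
3. Separate stopping study treatment from leaving the trial. State that primary-outcome data continue to be collected after treatment stops or compliance fails, where this is still possible and the patient consents. When treatment stops is a clinical matter and is not addressed here.
4. Replace the selectively used last observation with one pre-specified primary method, for example a likelihood-based repeated-measures model or multiple imputation.
5. Add a sensitivity analysis that varies the missing-data assumption, for example by shifting the imputed values by a stated amount in each arm. Keep the per-protocol analysis as supportive only.

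The cost is wording and slightly more analysis work, with no new patients. The main limit is item 3: Trial status says that recruitment is complete, so outcomes for patients already removed may be only partly recoverable. Items 1, 2, 4 and 5 do not depend on it.

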### Sample size calculation

Based on the literature and findings from a small pilot study that used metabolomic techniques, the sensitivity and specificity required to classify the control and PCOS groups will be 100% and 86%, respectively. The corresponding values between the control group and subgroup 1 will be 96.7% and 100%, respectively, while those between the control group and subgroup 2 will be 100% and 86.2%, respectively. The sensitivity and specificity for dividing PCOS into two different subtypes will be 90.9% and 87.5%, respectively. To meet the lower statistical limit, each subgroup will include at least 30 participants.

According to a presumptive maximum dropout tolerance of 20%, with a significance level of 0.05 and a power of 0.80, we calculate the required sample size for the experimental groups to be 216. In this trial, 60 people will be assigned to the healthy control group and 108 people to each experimental group across the three centers.

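### Last-observation carry-forward is to be used "selectively" with no rule, beside an unnamed imputation method; the exposure is mainly secondary indices and patients without a week-26 value

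*Protocol article*

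**What the plan says.** The Statistical analyses section of the protocol contains four relevant statements.

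- On method: "For missing data, we will employ the imputation adjustment approach", followed in the same sentence by "the last observation analysis will be selectively used to handle the missing data". The first half names no model; the second names a method but no rule for applying it.
- On the main analysis: "the FAS will be used for the basic analysis".
- On membership of that set: "participants who miss the primary outcome evaluation will be excluded".
- On robustness: "A sensitivity analysis will then be used to compare the results of the per-protocol analysis and the different intervention analyses". The stated purpose is to judge the impact of missing data, but no different assumption about the missing values is given.

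On timing, treatment lasts 6 months, while Study design says results are evaluated after three treatment sessions (3 months). Outcome measurements names the LH/FSH ratio as the main index without tying it to a visit. Under Clinical index group, "blood samples will be collected three times (week 0, week 15 ± 1, and week 26 ± 1"), for metabolomic evaluation. The sample size section allows for dropout: "According to a presumptive maximum dropout tolerance of 20" per cent.

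**The concern.** Carry-forward replaces a missing final value with an earlier one. A week-15 value carried to week 26 assumes that nothing changes over the last 26 − 15 = 11 weeks. A carried baseline value assumes exactly zero change. Neither estimates what 6 months of treatment does, and a single imputed value enters the analysis with the weight of a measurement.

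The word "selectively" adds a second problem. With no rule, carry-forward may be used for some indices or patients and something else for others, and the choice can be made after results are visible.

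Missing final values are foreseeable. The plan tolerates 20% dropout, and its safety outcomes include "inability of the patient to tolerate symptoms (e.g., nausea and vomiting caused by metformin"). The randomised arms differ in how patients are subtyped, and subtype decides the drug. Drug-related dropout can therefore differ between arms, although the documents give no figure for either arm's share of each drug.

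**Working it through.** **The plan's own figure.** The total of 216 cannot be rebuilt, because no between-arm effect or SD is stated, and nothing below depends on rebuilding it. The plan's inputs used here are 108 per arm, 20% dropout and two-sided testing at 0.05. The rest are assumptions, labelled as such.

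**Step 1: who can receive a carried value.** This depends on which visit is the primary evaluation.

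- (a) If it is week 26, anyone without a week-26 evaluation leaves the FAS. Nothing is carried forward for dropouts; only isolated missing items on secondary indices remain.
- (b) If it is the 3-month evaluation, taken here as the week-15 visit, earlier leavers are excluded. Those who leave later stay, and a mid-course value can be carried to week 26. Baseline would be carried only for a secondary index with no later value.

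**Step 2: equal, random dropout.** Let d = 0.20 be total dropout, e the share of dropouts leaving before week 15, and f the share of the week-26 arm difference already present at week 15 (e and f assumed).

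Under (b), the set is 1 − d·e of those randomised, and the ratio of estimated to true difference is

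[(1 − d) + d(1 − e)f] / (1 − d·e).

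- e = 0.5, f = 0.5: (0.80 + 0.10 × 0.5) / 0.90 = 0.889 + 0.111 × 0.5 = 0.944.
- e = 0.5, f = 1: 0.889 + 0.111 = 1.00.
- e = 0 (all leave late): 0.80 + 0.20f, which is 0.90 at f = 0.5 and 0.95 at f = 0.75.
- e = 1 (all leave early): everyone concerned is excluded, nothing is carried, and the ratio is 1.00.

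If the exclusion were not applied, the ratio would be (1 − d) + d(1 − e)f. At e = 0.5, f = 0.5 that is 0.80 + 0.20 × 0.5 × 0.5 = 0.85.

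**Step 3: unequal dropout.** Assume mean changes of 1.0 and 1.427 SD (a true difference of 0.427 SD, which 86 completers per arm detect with 80% power). Let 10% of one arm and 30% of the other lack week 26, and carry a half-way value. Each arm's mean is multiplied by (1 − m) + 0.5m, that is 0.95 at m = 0.10 and 0.85 at m = 0.30.

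- Better arm loses 30%: 1.427 × 0.85 − 1.0 × 0.95 = 0.263; 0.263 / 0.427 = 0.62 of the truth.
- Other arm loses 30%: 1.427 × 0.95 − 1.0 × 0.85 = 0.506; 0.506 / 0.427 = 1.18 of the truth.

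With no true difference and a common 1 SD improvement, the same split creates a spurious 0.95 − 0.85 = 0.10 SD. At 108 per arm this is 0.10 / √(2/108) = 0.735 standard errors, giving a two-sided type I error of about 11%. With equal missingness it stays at 5%.

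**Step 4: choosing between methods.** In simulation under the null (20,000 trials, 108 per arm, 20% random dropout split evenly around week 15, assumed visit correlations 0.5 to 0.6), each method alone rejects about 5%. Reporting the smaller of the carry-forward and available-case p-values rejects about 6.5%, and up to 6.9% in a repeat run. Excluding the early leavers, as in (b), leaves the result within that range.

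**The case against.** The strongest reply is that the FAS rule blocks most of the harm. It largely succeeds. A reader might infer that early dropouts enter as "no change" and that the estimate shrinks to 0.80 or 0.85 of its true size. Under either reading in Step 1, those patients are not in the main analysis set. For the same reason, patients who stop early with metformin intolerance are excluded, not carried forward at baseline.

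A reader might also infer that the arm difference is always pulled toward zero. That holds only for equal dropout with f below 1. Step 2 shows no attenuation at f = 1, and Step 3 shows movement in both directions.

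Three further points carry weight.

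- Weeks 0, 15 and 26 are documented as metabolomic sampling times. The clinical-index schedule is in a figure not shown, so which value would be "last" for a given index cannot be settled here.
- Carry-forward is not the only approach mentioned, although it is the only one identifiable.
- Under Blinding, the statistician is blinded until data lock, which limits choice by arm. It does not prevent choice by index or method, and it does not replace a rule.

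It can also be said that an analysis plan may supply the detail. That would answer an omission, but the published text goes further: it commits to carry-forward and makes its use discretionary.

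**Conclusion.** The point holds in limited form. The plan commits to a method that does not estimate a 6-month effect, leaves its use to discretion, and names no alternative assumption against which to test it. The reach is mainly secondary indices, plus patients with a 3-month evaluation but no week-26 value.

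Under reading (b) the attenuation is about 6% (ratio 0.94) in the illustrative case, and between none and 10% for f from 0.5 to 1. Under reading (a) it is nil for dropouts. The 15% loss (ratio 0.85) would apply only if the FAS exclusion were not enforced. Unequal dropout could matter more and in either direction, but the 10%/30% split is an assumption with no support in the documents beyond the overall 20%. The rise in type I error to about 6.5% requires that the smaller p-value actually be chosen.

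The sentence should be changed. The documents do not support a claim that the primary result is seriously biased by carry-forward.

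**What to change.** In the Statistical analyses section, and in any analysis plan:

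1. Replace the missing-data sentence. Remove selective carry-forward and state one named primary method in place of the unnamed imputation approach.
2. State the visit at which the primary outcome is evaluated, reconciling the 3-month evaluation with the 6-month treatment period.
3. Define the FAS as all randomised patients with at least one post-baseline value, instead of excluding those who miss the primary evaluation. Without this, under reading (a), patients seen only at mid-course stay out of the analysis and the model in item 4 cannot use them.
4. Analyse every quantitative index in the two randomised arms with the same mixed model for repeated measures on the scheduled post-baseline visits, with terms for arm, visit, arm by visit and baseline value.
5. If carry-forward is kept, make it a labelled sensitivity analysis applied to all patients and indices alike.

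The cost is wording and some programming: no extra patients, visits or assays. The model relies on data being missing at random, and its standard errors will be somewhat wider than carry-forward suggests.
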